## **1.5 HQP1351 Clinical Overview**

As of February 2021, HQP1351 has undergone a total of 9 clinical studies, including 3 Phase I studies (SJ-0002, SJ-0003 and HQP1351CU101), 3 clinical pharmacology studies [HQP1351LC104, HQP1351XC105 and HQP1351XC106 (in healthy volunteers)] and 3 Phase II pivotal studies (HQP1351CC201, HQP1351CC202 and HQP1351CC203). All studies were conducted in China except for HQP1351CU101 and HQP1351XC106 which were conducted in the United States. The Phase I clinical study of HQP1351 for GIST (SJ-0003) is ongoing in Chinese mainland. A total of 36 GIST subjects were enrolled as of January 31, 2021, and treated with HQP1351 orally QOD in 4 dose groups: 3 in the 20 mg dose group, 11 in the 30 mg dose group, 11 in the 40 mg dose group, and 11 in the 50 mg dose group, in 28-day cycles. All subjects were TKI-resistant GIST subjects who had previously been heavily treated. The Phase I study is currently actively enrolling subjects. Of the 36 GIST subjects, 28 have completed at least one efficacy assessment. The results are as follows: 10 subjects had stable disease (SD) and 18 subjects had progressive disease (PD).

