### 3.2 Exclusion Criteria

Subjects who meet any of the following criteria are not eligible for this study:

1. Subjects who have received antitumor cytotoxic chemotherapy, biologic drug therapy (such as monoclonal antibodies), immunotherapy (such as interferon), or radiotherapy within 28 days prior to the first dose or less than 5 times the half-life.
2. Subjects who have received tyrosine kinase inhibitor (TKI) treatment within 14 days prior to the first dose.
3. Subjects who have received other study drugs within 14 days prior to the first dose.
4. Subjects who have not recovered from adverse events (except alopecia) ( $>$  NCI-CTCAE v4.03 grade 1) due to prior treatment.
5. Malabsorption syndrome or other diseases affecting oral drug absorption.
6. Clinically significant, uncontrolled, or active cardiovascular diseases, including but not limited to history of myocardial infarction; history of unstable angina; history of congestive heart failure or left ventricular ejection fraction (LVEF) below the lower limit of normal within 6 months; history of atrial arrhythmia judged by the investigator to be of important clinical significance; history of ventricular arrhythmia, etc.
7. Hypertension inadequately controlled by antihypertensive drugs (systolic pressure  $>150$  mmHg or diastolic pressure  $>90$  mmHg).
8. Subjects who need to take drugs that has a known potential to cause ECG QT prolonged.
9. Pulmonary arterial systolic pressure  $>35$  mmHg as indicated by Echocardiography.
10. Subjects who have serious cardiovascular diseases during prior TKI use.

[figure not shown]

11. Hypertriglyceridemia that is difficult to control.
12. Major surgery, open biopsy (except intravenous catheter placement or bone marrow biopsy), or major traumatic injury within 14 days prior to the administration of study drug.
13. Arterial thrombosis or embolic events such as cerebrovascular accidents (including transient ischemic attacks), or pulmonary embolism or venous thrombosis events within 6 months prior to the administration of study drug, such as deep vein thrombosis within 3 months prior to the administration of study drug.
14. Subjects who require concomitant immunosuppressive therapy, other than corticosteroids prescribed for a short course of therapy.
15. Subjects with brain metastases.

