The study is initially designed as a Phase I study with standard 3+3 dose escalation. Based on the study results of HQP1351 SJ-0002 in CML patients and the consensus reached at the SJ-0003 kick-off meeting with the investigator, this study will explore the safety in the 30 mg, 40 mg, and 50 mg dose groups in parallel, and 10 subjects will be enrolled by means of randomization at each dose level using the IWRS. After preliminary adult data are available, adolescent subjects with advanced and/or metastatic wild-type GIST will be included. The dosage for adolescents is based on the adult dose and the selected dose will be adjusted according to their body weight. If the subject's body weight is  $\geq 40$  kg, the dose of 40 mg QOD will be given based on the adult dose. If the subject's body weight is  $\geq 30$  kg and  $< 40$  kg, the dose of 30 mg QOD will be given. If the subject's body weight is  $\geq 20$  kg and  $< 30$  kg, 20 mg QOD will be given. Based on the safety data from 9 clinical studies that have been conducted with HQP1351 and the safety and efficacy data of 36 patients already enrolled in this study, 40 mg QOD is selected as the dosage for non-randomized adult subjects after discussion between the investigator and the sponsor.

HQP1351 tablets will be administered orally to eligible subjects once every 2 days in a 28-day cycle. Subjects will receive treatment until PD, intolerable toxicity, death, or termination of treatment for any other reason. If a subject is assessed to have PD according to the RECIST v1.1 criteria, but the investigator determines that the subject will benefit from continuing the

[figure not shown]

study, then the subject may continue to take HQP1351 and undergo safety follow-up yet no more efficacy follow-up after PD is documented. During medication, subjects will not receive other antitumor study drugs, marketed drugs, or treatment methods other than HQP1351. Symptomatic (including those directed at controlling symptoms resulting from the patient's malignancy) and supportive treatments are allowed.

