## 7.9 Exploratory Biomarker Study

- 1) Tumor tissue samples will be collected from all subjects at baseline (i.e., from the screening period until the first dose of HQP1351 in Cycle 1), at PD, or at the EOT for assessment of mutations and/or expression profiles of KIT, PDGFRa, and other tumor-associated genes.
  - Tumor tissue sample collection at baseline: Newly acquired tissues should be preferred, and archival tissue samples (paraffin-embedded blocks or paraffin sections) may be provided if newly acquired tissues are not available.
  - Tumor tissue sample collection at PD or at the EOT: Tumor tissue samples will be collected by fresh puncture or tissue core biopsy (approximately > 3 mm) from patients who voluntarily cooperate with tumor biopsy.
- 2) In this study, 10 ml of whole blood will be collected from all subjects for ctDNA sequencing at baseline, during treatment (before administration on C3D1), at PD, or at the EOT to assess changes in KIT, PDGFRa, and other tumor-associated gene mutation ratio (MAF).

Sample collection time point for exploratory biomarker analysis is shown in Table 6. Detailed methods for collection, processing, labeling and transportation of samples for exploratory biomarker study are presented in the Central Laboratory's Manual for Study Reference.

[figure not shown]**Table 7: Sampling Time Point for Exploratory Biomarker**

|                                 | Baseline
(Day -28 to pre-dose on C1D1) | Pre-dose on
C3D1 | At PD or at the
EOT |
|---------------------------------|-------------------------------------------|---------------------|------------------------|
| Tumor tissue                    | X                          |                     | X          |
| ctDNA
(10 mL of whole blood) | X                                         | X       | X                      |

1. Newly acquired tissues should be preferred, and archival tissue samples (paraffin-embedded blocks or paraffin sections) may be provided if newly acquired tissues are not available.
2. Optional.
3. All blood sampling should be performed before HQP1351 administration.

[figure not shown]**Table 8: Schedule of Assessments**

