14. Premenopausal women of childbearing potential must have a negative pregnancy test within 7 days before the treatment.
15. Tumor imaging assessment: Assessments of tumor response will be performed during the screening period (within 3 weeks prior to the first dose), within 7 days prior to Day 1 of Cycles 3, 5 and odd-numbered cycles thereafter, and at the EOT (if it is > 28 days from the last assessment). All responses [PR and CR] must be confirmed by a repeat assessment not less than 4 weeks and theoretically not later than 5 weeks after the response criteria are met for the first time. During the follow-up period after discontinuation, subjects who have discontinued HQP1351 before PD will be assessed for tumor response every 8 weeks (visit time window +/-5 days) until PD or the start of other antitumor therapy, unless the subject voluntarily withdraws from the study. The same assessment method should be used at baseline and subsequent visits. If a subject experiences dose adjustment or interruption, the frequency of imaging examinations or scheduled imaging dates should not be changed. If there are clinical indications, a bone scan may be performed during screening.
16. The baseline collection time is from the screening period to the first dose of HQP1351 in Cycle 1. Sample collection time point for exploratory biomarker analysis is shown in Table 6.
17. PK blood samples will be collected from the first 3 adult subjects in each dose group, and PK blood samples will be collected from all non-randomized adult subjects receiving a fixed dose of 40 mg QOD. PK samples collected from adult subjects at each time point will be about 4 ml. PK sampling time points are shown in Table 5a. PK blood samples will be collected from all adolescent subjects. About 2 ml of blood sample needs to be collected at each PK time point. The PK blood collection time points are shown in Table 5b.
18. AEs will be collected from the time when the subject signs the ICF to 30 days after the last dose.
19. If the laboratory results at screening are within 7 days prior to the first dose of HQP1351, the test will not be repeated on C1D1.

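### The baseline ctDNA window (Day -28 to pre-dose C1D1) overlaps permitted prior-TKI use, so the exploratory change in mutation fraction starts from baselines that are not comparable between subjects

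*Protocol*

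**What the plan says.** Protocol section 7.9, item 2, plans "ctDNA sequencing at baseline, during treatment (before administration on C3D1), at PD, or at the EOT". The purpose is "to assess changes in KIT, PDGFRa, and other tumor-associated gene mutation ratio (MAF").

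Two places set the baseline window. Table 7 gives "Day -28 to pre-dose on C1D1" and marks ctDNA in that column. Table 8 footnote 16 says: "The baseline collection time is from the screening period to the first dose of HQP1351 in Cycle 1". The visit lists are narrower:

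- Section 7.2.2 puts the biomarker samples in the 28-day screening list and not in the 7-day list.
- Section 7.3.1 (C1D1) has no biomarker item.
- Table 8 marks the baseline blood sample only in the Day -28 to -1 column.

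Exclusion criterion 2 in section 3.2 rules out "Subjects who have received tyrosine kinase inhibitor (TKI) treatment within 14 days prior to the first dose". Section 1.5 describes the 36 GIST subjects enrolled by 31 January 2021: "All subjects were TKI-resistant GIST subjects who had previously been heavily treated". Dosing is "once every 2 days in a 28-day cycle" (section 4.1), which places C3D1 56 days after C1D1.

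**The concern.** A change score needs a baseline that reflects the state just before HQP1351 starts. Here the collection window is twice as long as the TKI washout. Two compliant subjects can therefore supply different baselines: one drawn while the previous TKI is still being taken, followed by at least 14 days without it, and one drawn after washout, immediately before the first dose. For the first subject, the difference between baseline and C3D1 contains the effect of stopping the old drug, the untreated interval and the effect of HQP1351, and these cannot be separated.

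Nothing else in the protocol closes the gap. No section requires the prior TKI to have stopped before consent, before screening or before this draw. The ban on other antitumor drugs in section 4.1 applies during HQP1351 medication. No second pre-dose ctDNA sample is scheduled. By contrast, Table 8 footnote 6 ties baseline vital signs to the pre-dose measurement on C1D1.

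What is at stake is the interpretation of the on-treatment molecular change. A later analysis can set affected samples aside, but it cannot supply a post-washout value that was never drawn.

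**Working it through.** The protocol states no figure for the ctDNA change, so there is none to reproduce. The check is day arithmetic followed by an illustration.

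**Inputs.** Baseline window Day -28 to pre-dose C1D1 (Table 7, Table 8 footnote 16); no TKI within 14 days before the first dose (section 3.2, criterion 2); 28-day cycles (section 4.1). There is no Day 0, and visit windows are ignored.

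**Overlap with prior TKI.** The days from -28 to -1 number 28. A TKI taken through Day -15 covers Days -28 to -15, which is 14 days: 14/28 = 50%. If Day -14 itself is read as allowed, the overlap is 15/28 = 54%.

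**Interval to C3D1.** C1D1 to C3D1 is 2 × 28 = 56 days. A Day -28 draw adds 28 days: 28 + 56 = 84. The share of that interval before HQP1351 is 28/84 = 33%.

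**Illustration (assumed values throughout).** Let g be the factor by which MAF changes between the draw and the first dose, and h the factor on HQP1351 from C1D1 to C3D1. The observed ratio is g × h. Take h = 0.5, a true 50% fall.

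Assume that untreated MAF doubles every T = 28 to 56 days, so that g = 2^(untreated days / T). After an on-TKI draw there are 14 untreated days if the TKI continues to Day -15, and 28 if it stops on the day of a Day -28 draw.

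| Untreated days | T (days) | g | g × 0.5 | Apparent fall |
|---|---|---|---|---|
| 14 | 56 | 2^0.25 = 1.19 | 0.59 | 41% |
| 14 | 28 | 2^0.5 = 1.41 | 0.71 | 29% |
| 28 | 56 | 2^0.5 = 1.41 | 0.71 | 29% |
| 28 | 28 | 2^1 = 2.00 | 1.00 | 0% |

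The range is 0% to 41% against a true 50%. The 0% end is an extreme corner: it needs the fastest assumed doubling and a TKI stopped on the day of the earliest permitted draw.

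**Direction.** The documents do not fix the sign. With g = 0.8 the observed ratio would be 0.8 × 0.5 = 0.40, an apparent fall of 60%. With g = 1.0 there is no distortion.

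**After the change.** A pre-dose C1D1 draw has 0 days of overlap with permitted TKI use, and the nominal interval is 56 days for every subject.

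**The case against.** The strongest reply is that this matters little.

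- The named exploratory endpoint (synopsis and section 10.2.3) is mutations and/or expression profiles associated with efficacy, and a baseline profile can serve that without any change score. Change in MAF appears only in section 7.9.
- Prior antitumor treatments and all medication in the 28 days before the first dose are recorded (section 7.2.2), so on-TKI draws should be identifiable, and handling them is ordinary content for an analysis plan that is not shown. Collection details also sit in a laboratory manual that is not shown.
- GIST subjects must be resistant to imatinib or have failed TKI treatment, so strong suppression by the previous TKI, which a rebound would require, cannot be presumed.
- The tables expressly permit a draw on C1D1.

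All of this limits the size of the point. It does not remove it: section 7.9 does plan the change, and a missing post-washout sample cannot be reconstructed.

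Some stronger readings are tempting but unsupported:

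- *ctDNA is the trial's only serial molecular read-out.* Tumor tissue is also planned at baseline and at PD or EOT, although Table 7 makes it optional. ctDNA is the only non-optional serial sample and the only on-treatment one.
- *A rebound after TKI withdrawal will be counted as failure of HQP1351.* No section defines ctDNA response, suppression or failure.
- *Half of the subjects are affected.* The 50% is calendar overlap; the number sampled on a TKI is not given.
- *The sample is always a screening draw.* The visit lists prompt it only there, but a later draw is compliant.
- *The progression sample has the same fault.* Section 7.9 and Table 7 already name PD; the weakness is that Table 8 marks only EOT.

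**Conclusion.** The point holds as a modest design weakness. A compliant baseline ctDNA sample can be drawn on the previous TKI, and the nominal interval to C3D1 varies from 56 to 84 days, so baselines are not comparable between subjects. This follows from the protocol's own windows and needs no assumption. The size and direction of any resulting distortion, and the number of subjects involved, are not in the documents; the 0% to 41% range rests entirely on the assumed 28- to 56-day doubling and on 14 to 28 untreated days. The measure is exploratory. The safety and RP2D objective and the RECIST endpoints are unaffected. It is worth correcting because the correction is cheap and the lost information cannot be recovered later.

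**What to change.** For subjects still to be enrolled, take the 10 mL baseline ctDNA tube pre-dose on C1D1 in place of the screening tube. Amend Table 7, Table 8, its footnote 16 and section 7.3.1 to match. Leave tissue collection and the TKI washout as they are.

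For subjects already sampled, use the recorded prior-TKI dates to flag baseline draws made less than 14 days after the last TKI dose. Summarise the change in MAF with and without the flagged subjects.

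As a minor separate point, mark the progression sample in Table 8 at PD as well as at EOT, in line with section 7.9 and Table 7. Section 4.1 allows treatment beyond PD, so the two dates can differ.

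**Cost.** There is no extra visit or blood volume: non-randomized adults and adolescents already have a pre-dose PK draw on C1D1. The change needs an approved amendment (section 15.2). A missed C1D1 tube cannot be redrawn. Two baseline conventions will coexist, since 36 of about 50 to 60 planned subjects were enrolled by 31 January 2021, leaving about 14 to 24 at that date.

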## 8 Efficacy Assessments

Assessments of tumor response will be performed during the screening period (within 4 weeks before the first dose), every 8 weeks after the first treatment (allowing imaging collection up to 7 days before the scheduled efficacy assessment), and at the EOT visit (if it is > 28 days from the last assessment). In any case, if the dosing regimen is adjusted, the visit schedule for efficacy assessment will remain unchanged in accordance with Table 7.

During the follow-up period after discontinuation, subjects without PD will be assessed for tumor response every 8 weeks (visit time window +/-5 days) until PD or the start of other antitumor therapy, unless the subject voluntarily withdraws from the study.

### 8.1 Response Evaluation Criteria in Solid Tumors (RECIST)

The response in solid tumor patients will be evaluated once every 2 cycles (i.e. 8 weeks) as per the latest version of Response Evaluation Criteria in Solid Tumors: Revised RECIST v1.1 (Eisenhauer, 2009) .

#### 8.1.1 Measurable lesions

**Tumor lesions:** Must be accurately measured in at least one dimension (longest diameter in the plane of measurement is to be recorded) with a minimum size of:

- 10 mm by CT scan (CT scan slice thickness no greater than 5 mm);
- 10 mm caliper measurement by clinical exam (lesions which cannot be accurately measured with calipers should be recorded as non-measurable);
- 20 mm by chest X-ray;
- 15 mm by traditional techniques (medical photography [skin or mouth lesions], palpation, plain film X-rays, CT or MRI). The shortest axis of measurable lesions should be at least double of the reconstruction interval (e.g., if reconstruction interval is 10 mm, the shortest axis of measurable lesions should be 20 mm) by CT scan; or
- $\geq 10$  mm by spiral CT scan.

**Malignant lymph nodes:** To be considered pathologically enlarged and measurable, a lymph node must be  $\geq 15$  mm in short axis when assessed by CT scan (CT scan slice thickness recommended to be no greater than 5 mm). At baseline and in follow-up, only the short axis will be measured and followed.

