#### **8.1.5.1 CT and MRI**

CT is the best currently available and reproducible method to measure lesion(s) selected for response assessment. This guideline has defined measurability of lesions on CT scan based on the assumption that CT slice thickness is 5 mm or less. When CT scans have slice thickness greater than 5 mm, the minimum length for a measurable lesion should be twice the slice thickness. MRI is also acceptable in certain situations (e.g., for body scans). More details concerning the use of both CT and MRI for assessment of objective tumor response evaluation are provided in the literature published by Eisenhauer in 2009.

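### Section 8.1.1 gives conflicting minimum sizes for non-nodal measurable lesions, so some response categories can depend on which item a site follows

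*Protocol*

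**What the plan says.** Section 8.1.1 gives five minimum sizes for non-nodal lesions, in this order:

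1. CT: "10 mm by CT scan (CT scan slice thickness no greater than 5 mm".
2. Clinical examination: "10 mm caliper measurement by clinical exam (lesions which cannot be accurately measured with calipers should be recorded as non-measurable".
3. Chest film: "20 mm by chest X-ray".
4. Older techniques: "15 mm by traditional techniques (medical photography [skin or mouth lesions], palpation, plain film X-rays, CT or MRI". The same item adds a rule for thick slices: "The shortest axis of measurable lesions should be at least double of the reconstruction interval". Its example is a 10 mm interval, which requires 20 mm.
5. Spiral CT, joined to item 4 by an 'or': at least 10 "mm by spiral CT scan".

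Three other sections bear on the same question. Section 8.1.2 treats non-nodal lesions as small only when the longest diameter is below 10 mm, and names no technique. Section 8.1.5.1 says: "When CT scans have slice thickness greater than 5 mm, the minimum length for a measurable lesion should be twice the slice thickness". Section 8.1.5.2 allows clinical lesions as measurable only when superficial and at least 10 mm by calipers.

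Section 8.1.6.2 then takes measurable lesions as target lesions, up to five in total and two per organ. Section 8.1.7.1 derives PR and PD from the sum of their diameters.

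**The concern.** Whether a lesion is measurable decides whether its diameter enters the baseline sum, and every later percentage change is taken against that sum or its lowest value. If two items in one list give different answers for the same lesion, two sites can follow the protocol faithfully and still assign different response categories to identical scans. Section 10.4.2 analyses ORR, CBR, DOR and PFS on the investigator's evaluation, and the protocol specifies no central read that would even this out. The groups are small (about 10 per randomized dose, 10-20 in the non-randomized part), so one changed patient is visible in the ORR. Sections 4.4 and 10.4 also use efficacy, together with safety and PK, in choosing the Phase II dose.

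**Working it through.** **Step 1. Set the items side by side.**

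| Lesion | Measurable under | Not measurable under |
|---|---|---|
| 10-14 mm, non-spiral CT, slices 5 mm or less | 8.1.1 item 1 (10 mm) | 8.1.1 item 4 (15 mm) |
| 10-14 mm, spiral CT, slices 5 mm or less | items 1 and 5 (10 mm) | no conflict if item 4 means conventional CT |
| 15-19 mm on chest film | item 4, as a plain film (15 mm) | item 3 (20 mm) |
| 15 mm or more by palpation or photography, not measurable by calipers | item 4 | item 2 and 8.1.5.2 |

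MRI has a non-nodal size only in item 4. The nodal rule (15 mm short axis) is stated consistently.

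**Step 2. Thick slices.** Take the protocol's own 10 mm example and assume that reconstruction interval equals slice thickness. Section 8.1.1 requires a shortest axis of 2 x 10 = 20 mm. Section 8.1.5.1 requires a length of 2 x 10 = 20 mm. Any lesion with a longest diameter of at least 20 mm and a shortest axis below 20 mm passes 8.1.5.1 and fails 8.1.1.

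**Step 3. Effect on the response category.** The protocol states no figure to reproduce here and gives no lesion measurements. The diameters below are assumptions for illustration. In each case the baseline sum is the smallest sum on study, there are no new lesions, and a lesion left out of the sum is followed as non-target without progression.

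Change = (follow-up sum - baseline sum) / baseline sum. From 8.1.7.1, PR needs a fall of at least 30%; PD needs a rise of at least 20% and at least 5 mm.

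| Assumed CT lesions (mm) | Small lesion counts (10 mm rule) | Small lesion excluded (15 mm rule) |
|---|---|---|
| 40+14 to 28+14 | (42-54)/54 = -22.2%, SD | (28-40)/40 = -30.0%, PR |
| 40+12 to 27+12 | (39-52)/52 = -25.0%, SD | (27-40)/40 = -32.5%, PR |
| 30+12 to 23+6 | (29-42)/42 = -31.0%, PR | (23-30)/30 = -23.3%, SD |
| 25+12 to 31+12 | (43-37)/37 = +16.2%, SD | (31-25)/25 = +24.0% and +6 mm, PD |
| 12 only, to 8 | (8-12)/12 = -33.3%, PR | no target lesion, Non-CR/non-PD |

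The category moves in both directions, so the ambiguity has no fixed sign. A PR counts towards ORR only if confirmed at least 4 weeks later (8.1.11).

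**Step 4. What one changed response is worth.** These are exact 95% intervals, as 10.4.2 specifies:

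- n = 10: ORR moves from 0% (0 to 30.8%) to 10% (0.3 to 44.5%).
- n = 20: from 0% (0 to 16.8%) to 5% (0.1 to 24.9%).
- In a dose group of 11, as enrolled by January 2021 (section 1.5), it is 1/11 = 9.1 points. Among the 6 wild-type subjects in section 1.6 it is 1/6 = 16.7 points.

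**The case against.** The best defence is that item 4 describes older methods: its label and its 10 mm interval point to conventional CT, and item 5 deals with spiral CT separately. This stands for spiral CT, which is 10 mm throughout. It does not clear item 1, which covers CT without restriction, so non-spiral CT with thin slices remains in conflict.

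A second defence is that the 'or' makes any one item sufficient. The CT minimum would then be 10 mm. But the 15 mm entry for CT would have no effect, the 20 mm chest film entry would be undercut by 15 mm for plain film, and palpation would still collide with the calipers-only rule.

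A third is that the side conflicts matter little. Section 8.1.5.2 is explicit on clinical lesions, 8.1.5 puts imaging ahead of clinical examination, 7.5.1 schedules CT, and 8.1.5.3 prefers chest CT to chest X-ray. This is fair, and it makes CT the main issue.

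Some stronger readings are tempting but not supported:

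- That 8.1.5.1 itself sets 10 mm. It prints no such figure, only the 5 mm slice assumption and the doubling rule.
- That 8.1.2 or 8.1.5 confirms 20 mm for chest X-ray. Neither gives a size for it.
- That the list contradicts the published RECIST v1.1. The protocol names that standard, but the publication is not at hand. The point rests on the protocol's internal conflict alone.
- That responses will often flip. A flip needs a lesion in the disputed size band, room under the size-ranked caps of five in total and two per organ, and a sum near a cut-off.

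**Conclusion.** The list in 8.1.1 is inconsistent as written, and no other section says which item prevails. For CT, the clear conflict is confined to lesions of 10-14 mm on non-spiral scans with slices of 5 mm or less. For chest film it covers 15-19 mm. The clinical and thick-slice rules conflict as well. The examples show that the category can change between SD and PR, SD and PD, or PR and Non-CR/non-PD. They rest on assumed diameters, and their frequency cannot be estimated from the protocol.

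The weight is modest. Only secondary, investigator-assessed ORR, CBR, DOR and PFS are affected. A reader might infer that the primary endpoint is compromised; it is not, because that endpoint is safety and tolerability. The link to the primary objective is indirect, through the use of efficacy in choosing the Phase II dose. The correction is worth making because it costs almost nothing and removes a source of difference between sites.

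**What to change.** Replace the non-nodal list in 8.1.1 with one threshold per technique:

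- CT: 10 mm with slices of 5 mm or less; otherwise twice the slice thickness, applied to the longest diameter, which is how the length rule in 8.1.5.1 is read here.
- MRI: an explicit threshold with the same slice rule.
- Clinical examination: 10 mm by caliper.
- Chest X-ray: 20 mm.

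Remove the item on traditional techniques and the separate spiral CT item. The first of these is the only place where MRI has a non-nodal size, so it must not be deleted without the MRI entry above. Align 8.1.2 (so that its small-lesion cut-off follows the technique thresholds), 8.1.5.1 and 8.1.5.2 with the new list. Leave the nodal rule as it is.

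The cost is protocol wording and a note to site radiologists.
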